### Intervention

For the intervention group, an intervention worker will provide a coherent package of needs-oriented discharge planning and monitoring focusing on the care process. The NODPAM intervention will apply principles of needs-led care (e.g. [34]) and focus on the inpatient-outpatient transition, with the intervention worker emphasising continuity of the care process vis-à-vis both patient and clinicians (e.g. [7]). The intervention worker will provide (and patients will be actively involved in) two manualised intervention sessions (each of about 45 minutes duration, see Figure 1, lower part):

#### Pre-discharge intervention session

The intervention worker obtains the relevant information of patients' met and unmet needs in a basic plan (results of the CAN rating) from the research worker. The first joint (pre-discharge) intervention session in general takes place seven days prior to hospital discharge with the following people participating: in-patient clinician, patient and carers if the patient wants to. There is a guided discussion of the critical domains of need identified on the basis of CAN ratings which require both current and post-discharge measures and/or interventions. The handwritten draft of the post-discharge treatment plan contains every addressed need with a precise problem definition, objectives, time-frame regarding goal attainment and persons responsible for the implementation. The treatment plan is signed by all participants. A typed version of the pre-discharge treatment plan will be sent to the outpatient clinician and the patient, and the accompanying letter will include the advice to discuss the plan and monitor its progress during every contact between them. The inpatient clinician is remunerated with CME credit points for each NODAPM intervention session and with a book voucher worth 50 € (once).

#### Post-discharge intervention session

Three months after discharge, the intervention worker arranges a second (post-discharge) intervention session including all stakeholders involved in the outpatient treatment phase: outpatient clinician, patient and relatives if the patient wants them to be present. Initially, a written protocol is drafted to summarise critical domains of need from the first session, their development since discharge, and the current CAN ratings (at 3-month follow-up). Participants are asked if they can name reasons for change (improvement or deterioration) or stability of ratings in the related domains.

Subsequently, a revised version of the pre-discharge treatment plan is developed on the basis of current met and unmet needs and signed by all participants. A typed version of the plan will be sent to the outpatient clinician and the patient with the advice that the plan should be continuously integrated in outpatient treatment, i. e. discussed and monitored during every contact between the outpatient clinician and patient for a period of at least three months. The outpatient clinician in private practice is remunerated with CME credit points and 100 € for each NODPAM intervention session.

### Statistical analysis

The primary endpoints will be derived from the difference in LOS and number of hospitalisations between T0 and T1, T2, and T3. The secondary endpoints will be calculated from the differences in sum (or – if applicable – subscale) scores of the secondary outcome measures between T0 and T1, T2, and T3. Multiple measurement points have been chosen in order to scrutinise the intervention's effect over time, especially the question of whether short- and mid-term effects would persist.

Analyses will start once baseline data have been collected and cleaned. Descriptives of all outcome measures will be produced, and outcome trajectories from T0 – T3 will be examined via exploratory analyses. The effect of the intervention on reduction of number of inpatient days as well as on clinical outcomes, quality of life, and compliance will be tested by means of random-effect regression models including a constant group effect across time [35-37]. Due to the application of a generalised least square (GLS) estimation weighted for the lengths of the time series for each case, these models allow the inclusion of cases with incomplete (unbalanced) data across panels. Due to expected skewness of the primary dependent variable (LOS), bootstrapping methods will be applied for the estimation of standard errors and confidence intervals. Cost-effectiveness of intervention will be tested by means of the net-benefit approach [38], and its cost-utility by using QALYs generated from EQ-5D.

Analysis will be carried out according to the principle of intention-to-treat. In case attrition should exceed the projected rate of 10%, additional per-protocol analysis will be performed.

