Probably due to large differences between psychiatric service systems, there is no consensus on what constitutes HU. In operationalising HU, most authors solely relied on an arbitrary number of readmissions during a given time period – usually study duration. An analysis of nine studies pertaining to psychiatric inpatient treatment (cf. table 1 in Kent et al. [9]) showed that a mean number of 3.25 (SD = 1.75) admissions during 2.38 (SD = 1.51) years, i.e. 1.37 admissions per year, was used as the criterion for HU. This corresponds to Roick et al. [10] who found that overall, patients with 1 – 3 inpatient stays during one year are identified as a high utilisers. This measure is easily accessible, but has also been criticised (e.g. [11]) since patients with multiple short hospital stays might be wrongly included (since they do not use excessive resources), and patients with few very long hospital stays might be wrongly excluded, especially when observation time is short. Thus, some authors used cumulated length of stay (LOS) during a given period (in addition to or instead of number of readmissions) to identify HU. E.g. Lucas et al. [12] developed a "heaviness of use" score by combining the frequency of admissions with the total number of bed days. Exceptionally, direct treatment costs beyond cumulated inpatient costs including costs for non-inpatient care (day hospital treatment, outpatient and complementary care) was applied [13], but data collection is laborious and might not be worthwhile since costs for inpatient care make up the largest share (75–92% [9,14]) of total treatment costs.

**Table 1 T1:** Study instruments by raters and measurement points.

	*T0*	*T1*	*T2*	*T3*
*Research worker*	CAN-EU	CAN-EU	CAN-EU	CAN-EU
	CSSRI-EU	CSSRI-EU	CSSRI-EU	CSSRI-EU
	BPRS	BPRS	BPRS	BPRS
	HAM-D	HAM-D	HAM-D	HAM-D
	MANSA	MANSA	MANSA	MANSA
	EQ-5D	EQ-5D	EQ-5D	EQ-5D
*Clinician*	GAF	GAF		
	CGI	CGI		
	STAR-C	STAR-C		
		ZUF-THERA		
		DP satisfaction		
*Patient*	SCL-90-R	SCL-90-R	SCL-90-R	SCL-90-R
	STAR-P	STAR-P	STAR-P	STAR-P
		ZUF-8		
		DP satisfaction		

*Notes*: DP = Discharge Planning. See text for other abbreviations.

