### Outcome measures

Assessment will take place at baseline and three (3, 6 and 18 months) follow-up measurement points in each participating centre (see Figure 1). Patients will receive a remuneration of 30 € for each assessment. Secondary outcomes will be provided by independent raters (research workers trained in study instrument use), clinicians, and patients. See Table 1 for an overview of the instruments used.

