#### Clinician perspective (T0 [inpatient clinician] and T1 [outpatient clinician])

*Psychosocial functioning *will be rated via the "Global Assessment of Functioning Scale" (GAF [23]) which has been shown to be a practical and valid instrument in psychiatric research [24]. Overall *psychological impairment *will be tapped into via the "Clinical Global Impression Scale" (CGI [25]). *Therapeutic relationship *(clinicians' point of view) will be assessed using a retranslated German version of the "Scale to assess the therapeutic relationship in community mental health care" clinician scale (STAR-C [26]).

*Satisfaction with therapeutic work in the ambulatory setting *(T1 only) will be covered with a self-developed scale (ZUF-THERA [27]) consisting of six rephrased items of the ZUF-8 [28], the German version of the "Client Satisfaction Questionnaire" (CSQ [29]). The items were rephrased in that way that outpatient clinicians could give an evaluation of the quality of the given treatment. *Satisfaction with discharge planning *(T1 and intervention group only) will be assessed with a self-developed nine item rating scale.

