#### Patient perspective (T0 – T3)

*Psychological impairment *will be measured using the German version [30] of Derogatis' [31] "Symptom-Check-List" (SCL-90-R), a widely used and validated self-report scale. *Therapeutic relationship *(patients' point of view) will be assessed using the "Scale to assess the therapeutic relationship in community mental health care" patient scale (STAR-P [26]). *Satisfaction with outpatient treatment *(T1 only) will be covered for the outpatient setting with the German version (ZUF-8 [28]) of the "Client Satisfaction Questionnaire" (CSQ [29]). *Satisfaction with discharge planning *(T1 and intervention group only) will be assessed with a self-developed eight item rating scale.

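### The single change-from-T0 rule for secondary endpoints does not fit seven of the 15 entries in Table 1, and subtracting T0 gives up precision, most where the T0 and T1 raters differ

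*Protocol article*

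**What the plan says.** The protocol article, Statistical analysis, defines the endpoints in one sentence that begins "The secondary endpoints will be calculated from the differences in sum" and ends with "scores of the secondary outcome measures between T0 and T1, T2, and T3". Subscale scores may replace sum scores. No instrument is exempted.

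The Outcome measures section says what counts: "Secondary outcomes will be provided by independent raters (research workers trained in study instrument use), clinicians, and patients". It refers to Table 1 ("Study instruments by raters and measurement points") for the list.

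The schedule is then narrower for some instruments:

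- GAF, CGI and STAR-C come under the heading "Clinician perspective (T0 [inpatient clinician] and T1 [outpatient clinician", and Table 1 leaves their T2 and T3 cells empty.
- ZUF-THERA: "T1 only) will be covered with a self-developed scale".
- ZUF-8: "T1 only) will be covered for the outpatient setting".
- Discharge-planning satisfaction, clinician form: "T1 and intervention group only) will be assessed with a self-developed nine item rating scale". The eight-item patient form has the same restriction.

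**The concern.** A change from T0 needs a T0 score, and a change at T2 or T3 needs a score at that visit. For several listed instruments one or the other was never scheduled, so the rule and the schedule contradict each other. Whoever runs the analysis must choose visits and contrasts that the text does not give, in a trial whose staff are not blinded.

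There is a second problem where a difference can be formed. For GAF and CGI the two scores come from different clinicians in different settings, so the difference mixes patient change with rater and setting change. For STAR-C the two scores describe two different therapeutic relationships, and the difference is change in neither. Subtracting such a T0 score adds noise that using it as a covariate would avoid.

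At stake are the readability and precision of the clinician-rated and satisfaction measures.

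**Working it through.** **Step 1: schedule against rule.** Table 1, checked against the Rater, Clinician and Patient perspective sections, has 15 instrument entries.

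| Entries | Scheduled visits | Differences that exist |
|---|---|---|
| CAN-EU, CSSRI-EU, BPRS, HAM-D, MANSA, EQ-5D, SCL-90-R, STAR-P (8) | T0, T1, T2, T3 | T1−T0, T2−T0, T3−T0 |
| GAF, CGI, STAR-C (3) | T0, T1 | T1−T0 only |
| ZUF-8, ZUF-THERA (2) | T1 | none |
| Discharge-planning satisfaction, clinician and patient forms (2) | T1, intervention group only | none, and no control data |

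So 3 + 2 + 2 = 7 of 15 entries cannot follow the rule. CSSRI-EU is among the eight that can, but it also carries the primary outcomes.

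The planned random-effect model accepts cases with incomplete panels. That deals with scores a patient failed to give; it does not supply a visit that was never scheduled. If the difference is the outcome, GAF, CGI and STAR-C give one value per patient, so there is no series over time to model.

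**Step 2: cost of subtracting T0.** Let the score have variance σ² at both T0 and T1 (assumption) and let ρ be the T0–T1 correlation within arm. The protocol gives no ρ, so a range is shown.

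- Change score: variance 2σ²(1−ρ).
- T1 score with T0 as covariate, large samples: variance σ²(1−ρ²) = σ²(1−ρ)(1+ρ).
- Ratio of the first to the second: 2/(1+ρ). The confidence interval widens by the square root of this.

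| ρ (assumed) | Variance ratio 2/(1+ρ) | Interval width ratio | Wider by |
|---|---|---|---|
| 0 | 2.00 | 1.41 | 41% |
| 0.3 | 1.54 | 1.24 | 24% |
| 0.5 | 1.33 | 1.15 | 15% |
| 0.7 | 1.18 | 1.08 | 8% |

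A change of rater tends to lower ρ, so the clinician scales are likelier to lie towards the upper rows.

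**Step 3: does the direction depend on equal variances?** With standard deviations s0 and s1, the change score has variance s0² + s1² − 2ρ·s0·s1 and the adjusted comparison s1²(1−ρ²). The first minus the second is (s0 − ρ·s1)², which is never negative. In large samples the adjusted comparison is therefore never less precise; only the size of the gain depends on the assumptions.

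**Step 4: bias.** T0 precedes the intervention and allocation is random, so the expected T0 score is the same in both arms. The switch from inpatient to outpatient clinician also occurs in both arms. The between-arm difference in change then has the same expected value as the between-arm difference at T1. The loss is in precision and interpretation.

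**The case against.** The best defence is that the sentence is a general statement in a condensed article. The exceptions are openly marked in the instrument descriptions, a sensible reader would apply the rule where the visits exist, and the contrast for each secondary instrument is usually left to an analysis plan, which is not shown here. This stands in part: the schedule mismatch alone is mostly a matter of wording. It does not remove the contradiction, because the rule is stated without limit and Outcome measures counts clinician and patient instruments as secondary outcomes. Nor does it answer the choice of subtraction over adjustment.

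It can also be said that the planned model may be fitted to the scores themselves, so that the ratio 2/(1+ρ) need not describe the final estimator. That is fair. The figures apply to the endpoint as the section defines it, namely a difference.

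Three stronger readings are tempting, and the protocol supports none of them.

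- A reader might infer that the clinician-scale differences give a wrong treatment effect. They do not, for the reason in Step 4.
- A reader might infer that the trial's clinical conclusions become uninterpretable. BPRS, HAM-D, SCL-90-R, MANSA and EQ-5D run from T0 to T3 and are rated by the research worker or the patient. Of the clinical-outcome measures only GAF and CGI are affected, and no stated hypothesis concerns therapeutic relationship or satisfaction.
- A reader might infer that STAR-P, like STAR-C, compares two relationships. The patient is an inpatient at T0, so this is possible, but the Patient perspective section does not say which clinician is rated then.

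Finally, the comparison must be a fair one. Against an unadjusted T1 comparison, the change score has 2(1−ρ) times the variance: worse below ρ = 0.5, equal at 0.5 and better above it. Quoting only low correlations would make the change score look worse than it need be. Against the T0-adjusted comparison it does not win at any ρ.

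**Conclusion.** The point holds as a conflict between rule and schedule, together with an improvement that needs no new data. That seven of 15 entries cannot follow the stated definition is certain from the protocol itself. For GAF, CGI and STAR-C, the one difference that can be formed mixes raters and settings and, for STAR-C, relationships. This makes it hard to read as change and costs precision without biasing the randomised contrast.

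The size of the loss, 8% to 41% in interval width for ρ from 0.7 down to 0, rests on an assumed correlation, equal variances at T0 and T1, and large samples. For instruments with the full schedule, replacing subtraction by adjustment is an efficiency gain and not the repair of an error. The matter concerns secondary endpoints only and deserves correction because the remedy is nearly free.

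**What to change.** Replace the single sentence in Statistical analysis with a statement of visits and contrast for each instrument:

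- **GAF, CGI, STAR-C:** compare arms at T1 with the T0 score as a covariate, not subtracted. State that the rater changes between the visits.
- **ZUF-8, ZUF-THERA:** compare arms at T1.
- **Discharge-planning satisfaction, both forms:** report descriptively for the intervention group.
- **CAN-EU, BPRS, HAM-D, MANSA, EQ-5D, SCL-90-R, STAR-P:** model T1 to T3 with T0 as a covariate, for efficiency. For STAR-P, also state which clinician the patient rates at T0.

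The cost is analysis wording only. No visit, instrument or sample-size change is needed. The wording should be fixed before outcome data are examined by arm.

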### Data monitoring and safety

All trial data will be stored safely at the participating centres. The CC is responsible for the merging of the data from the centres and – after data cleaning – redistributing it to the centres for analysis.

Data Monitoring will be carried out by persons independent of trial conduct. Before start of data collection, each participating centre will name a person responsible for data entry and monitoring to the CC. The following monitoring strategy will be adhered to.

#### Monitoring of patient recruitment, data collection and application of the intervention

Study visits and regular telephone conferences will allow for a 100% check of essential trial parameters. In particular, the CC will see to that: (a) All informed consent forms which have been signed by patients are complete and safely stored at the participating centres; (b) Every participating patient meets inclusion criteria; (c) Both the intervention and assessment of outcome criteria, in each individual patient, are carried out according to the trial protocol and intervention manual. In addition, before start of recruitment, trial staff responsible for data collection and application of the intervention will be trained in the use of study instruments at the CC, also by external experts if applicable. As the study progresses, adherence to instrument and intervention manuals will be continuously monitored and training refreshed if necessary, especially in case of staff changes.

#### Monitoring of flow and quality of data

(a) At each centre, data will be entered via identical templates programmed by CC staff using *EpiData *, a reliable software for entering and documenting data allowing for e.g. the definition of out-of-range and outlier data as well as logic checks; (b) After data entry, centres will send copies of data files and completed questionnaires to the CC which will carry out: (i) Review: 10% of the data will be entered again by the CC and subsequently compared with the data in the files received from the participating centres. In case of major differences, proportion of the reviewed data will be increased; (ii) Query: In case of mismatch, the CC will contact the respective participating centre in order to correct data problems. Results of these queries will be communicated to the group.

Furthermore, a trial steering committee (TSC) was established in its function as an independent board of members to provide overall supervision and protection for the trial participants and the principal investigators. In view of the non-invasive intervention, the risk for participating patients is considered marginal. Should, for any unforeseeable reason, the intervention or data collection place a burden on a given participant and should at the same time he or she be unwilling to terminate participation, the research worker and/or intervention worker are required to report this to the TSC who will then decide on whether or not the participant will have to be excluded. Such instances will be documented thoroughly.

The advisory board, the TSC and Ulm University Hospital will be continuously informed of study progress including data quality issues.

### Ethics

Patient confidentiality will be strictly maintained, i.e. by no means will publications contain person-related information. However, the conduct of a longitudinal trial requires patient follow-up. Thus, study participants' personal data (e.g. names and addresses) will be recorded for the duration of the trial. Patient ID data will be stored safely and kept separate from the data set used for analyses.

In the course of recruitment, the research worker will devote special attention to providing the patients with detailed information on the trial so they have a sound basis on which to decide on informed consent. It will be made clear to the patient that he or she can withdraw consent at any time during the course of the study without any consequences. In case the patient is under legal custody, the custodian's consent does not suffice. All participating centres' ethics committees will have issued positive votes on NODPAM before the start of the study.

## Discussion

There is broad consensus that relapse prevention is one of the major aims of aftercare. However, the success of attempts to reduce high re-hospitalisation rates in people suffering from severe mental disorders has been limited so far. Insufficient discharge planning and follow-up is considered one of the main reasons for limited community tenure and unfavourable clinical outcomes. Only a small number of RCTs have been conducted to test this assumption.

Literature reviews conclude that specific interventions targeting the needs of high utilisers and subsequently preventing unnecessary high service use should be developed and evaluated as to their use for patients and clinicians [9,10,39].

Furthermore, taking into account the finding that health service costs make up 76% of the total costs, and that 59% of these are inpatient costs [14], any intervention that is effective in reducing the heavy inpatient bed use of heavy users should have a substantial effect on the total service costs [12,38]. Since service use patterns of high utilisers appear to depend on service system rather than on individual patient variables [8], it has been specifically recommended to identify gaps in current service provision [9], and – as outlined above – discharge from psychiatric hospital obviously can be considered such a gap, particularly in fragmented service systems such as the German one.

If this needs-oriented discharge planning and monitoring intervention proves to be successful in this RCT, a tool will be at hand (a) to harmonise fragmented service provision, i.e. improve collaboration of in- and outpatient services and continuity of care; (b) to improve community tenure, clinical impairment, and quality of life; and (c) to reduce unnecessary inpatient treatment costs.

## Footnotes

1 These were: (a) Randomisation strata: Originally planned strata were centre, primary diagnosis, and GAF score at admission. GAF score at admission was replaced by gender and illness duration. (b) Original exclusion criterion was only that subjects with a primary diagnosis of substance abuse will be excluded. (c) Originally the Helping Alliance Questionnaire (HAQ) was intended to be used for the assessment of the quality of the therapeutic relationship (changed to STAR); (e) Application of instruments to assess treatment satisfaction (ZUF-8 and ZUF-THERA) and satisfaction with discharge planning; (d) Specification of details on amount and kind of clinician remuneration.

2 The CSSRI-EU also serves to assess necessary information pertaining to SES (work, financial and living situation) and service utilisation beyond inpatient care. Furthermore, basic patient data will be available via the "BADO" which has been implemented at all participating centres.
